### Design overview

This feasibility study will use a 2-week, interventional, independent measures research design (figure 1).

**Figure 1 F1:**
[figure not shown]
Trial schema of participant flow throughout the duration of the study.

A variation of a stepped-wedged design/rolling recruitment will be utilised, with the interventions being conducted multiple times over the course of several months in order to maximise the potential sample size due to constraints of the setting: a delayed transfer of care hospital ward for patients prior to official discharge, with the majority of patients residing on the ward for >3 weeks, and ~25 patients on the ward at any given time.

The independent variables of the study will comprise of two exercise training interventions: a specially adapted machine-based resistance training intervention, and Move It Or Lose It (MIOLI), an established community-based exercise intervention for older adults. A control group will be utilised within the proposed future clinical trial but will not be utilised within this feasibility study as one of the primary purposes of this study is to assess the feasibility, and to a limited degree the efficaciousness, of the interventions within this setting (figure 2).

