**Figure 2 F2:**
[figure not shown]
The independent variables of the proposed future clinical trial.

In order to ensure this present study is as scientifically valid as possible a number of precautions have been taken to protect the internal and external validity of the study within its methodological design: first, for each participant, all testing procedures (baseline and post-intervention (2 weeks)) will be conducted at approximately the same time of day (±2 hours). This will be controlled in order to protect the findings of the study from changes in the dependent variables which may be attributable to circadian variation rather than manipulation of the independent variables.^29^ The hypothesis of the study will not be divulged to participants prior to or during the conduction of the study in order to control for any potential degree of demand characteristics; a scenario where participants alter their behaviour and/or answers, in order to align with what they believe is potentially the ‘desired’ outcome of the study. All dependent variable testing sessions will take place at least 24 hours after the cessation of the previous training session for each participant. This will be implemented to ensure acute fatigue does not become a contributing factor to the results of the study, specifically relating to the secondary dependent variables, but also the feasibility of such practice during a proposed future clinical trial. The order in which dependent variables are tested will be counter-balanced throughout the study at each assessment timepoint in order to attempt to protect the study from practice effects, especially order effects, where a participant has been exposed to a specific order of testing before and as such performs better on subsequent testing procedures of the same material. Additionally, only one intervention will be run at a given time, protecting against potential subconscious selection bias among the research team relating to group allocation of participants. Finally, in order to increase the external validity of the study, eligibility criteria will be kept as minimalistic as possible (within the limits of safety and reason), in order to allow as inclusive a proportion of this population as possible, and in such producing findings which are applicable to not only those within the study, but to the greater population of frail geriatric hospital inpatients and particularly those within delayed transfer of care settings.

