### Interventions

All participants will undergo 10 sessions in total throughout the 2-week intervention in either one of the two interventions. All session will be conducted individually under the guidance of a qualified trainer. A maximum of one session will be performed each day, and sessions will not be performed on any more than a maximum of three consecutive days throughout the duration of the study (table 2).

**Table 2 T2:** Study timeline of all major events during each round of recruitment (SPIRIT schedule)

Week	Seated physical activity in ageing (SPAA) study timeline						
	Monday	Tuesday	Wednesday	Thursday	Friday	Saturday	Sunday
0	Identification + participant information sheet distribution	24 hours consideration period	Recruitment, eligibility screening and baseline assessments	Recruitment, eligibility screening and baseline assessments	Recruitment, eligibility screening and baseline assessments	Recruitment, eligibility screening and baseline assessments	–
1	Training	Rest	Training	Training	Rest	Training	Training
2	Training	Rest	Training	Training	Training	Rest	Training
3	Post-intervention assessment	Post-intervention assessment	Post-intervention assessment	Post-intervention assessment	Post-intervention assessment	Post-intervention assessment	–

SPIRIT, Standard Protocol Items: Recommendations for Interventional Trials.

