### Sample size

This study aims to recruit a convenience sample of n =~30 participants: 15 in each intervention. No formal power calculations were conducted due to the feasibility nature of this study. This sample size was based on initial expectations related to the obtainment of data saturation in the qualitative component of the study given its phenomenological approach.^50 51^

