#### Secondary dependent variables

Statistical analysis of the secondary dependent variables will be performed using IBM Statistical Package for Social Sciences (SPSS) software. These analyses will be performed as part of the limited efficacy testing regarding the potential impact of the interventions on the secondary dependent variables (proposed primary dependent variables of the future clinical trial). These analyse will provide an estimation of efficacy and provide valuable insight regarding feasibility; useful to informing the design of the future powered clinical trial. Specifically, the following statistical analysis will be utilised: 2×2 way independent measures analysis’ of variance consisting of two independent variables; the specially adapted resistance training intervention, and the MIOLI intervention, each with two levels: baseline and post-intervention. A subsequent post hoc test will be utilised if a significant main effect or interactions are found. Pearson product correlations will also be utilised between various sociodemographic variables (such as age and sex) and the dependent variables of this study, to assess possible relationships between differences in sociodemographic factors and changes in the dependent variables.

Central tendency and variability measurements consisting of parameters such as the mean, median and mode, and SD and range of scores, respectively, will also be utilised during the analysis of data for illustrative purpose. Significance levels will be set at 0.05 (p≤0.05), and effect sizes will be reported for all analyses. In order to establish if the assumptions of parametric statistics have been met regarding the assumption that there is a normal distribution of data, the data will be analysed for skewness and kurtosis. In the event, data do not fulfil the assumptions of parametric statistics, the non-parametric equivalent of the aforementioned statistical analysis will be employed, namely the Scheirer-Ray-Hare test, and Spearman’s rank-order correlations. As the quantitative component of this study has not been powered given the feasibility nature of the study, the examination of the efficacy of the intervention to impact these secondary dependent variables is limited; and interpretation of these results should be treated with caution pending the future powered clinical trial. All results will be reported with effect size and 95% CIs.

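### The intervention is allocated by recruitment round, but the planned test of one intervention against the other treats participants as independently allocated and has no round term

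*Protocol article*

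**What the plan says.** **Allocation.** The Design overview states: "A variation of a stepped-wedged design/rolling recruitment will be utilised, with the interventions being conducted multiple times over the course of several months". Later in that section, as a safeguard against selection bias, it says that "only one intervention will be run at a given time". Table 2, under Interventions, is captioned "Study timeline of all major events during each round of recruitment" and runs from week 0 to week 3. Whoever is recruited in a round receives that round's intervention.

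**Design label.** The Design overview opens: "This feasibility study will use a 2-week, interventional, independent measures research design". It also says: "A control group will be utilised within the proposed future clinical trial but will not be utilised within this feasibility study". The study has one ward, and no staggered move of units from one condition to another is described.

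**Analysis.** Statistical methods, Secondary dependent variables, specifies a 2×2 independent-measures analysis of variance on "the specially adapted resistance training intervention, and the MIOLI intervention, each with two levels: baseline and post-intervention". The fallback is the Scheirer-Ray-Hare test, the significance level is 0.05, and all results get 95% CIs. No round or period term is named.

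**Size and delivery.** Sample size: "This study aims to recruit a convenience sample of n =~30 participants: 15 in each intervention". Interventions: "All session will be conducted individually under the guidance of a qualified trainer".

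**The concern.** The unit that receives an intervention is the round. Participants in one round share a ward and a few weeks of calendar time, so their changes may be more alike than those of participants in different rounds. The between-intervention contrast is then a comparison of a few rounds with a few other rounds, and variation between rounds belongs in its error. A model with intervention and time alone leaves that variation out.

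At stake are the p-value and 95% CI of the only direct comparison of the two interventions. The article describes these analyses as informing the design of the later powered trial.

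A second fault affects the same contrast. Baseline and post-intervention values come from the same people, but an independent-measures 2×2 analysis treats them as separate samples. This distorts the error term in the opposite direction, so the two faults have to be considered together.

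**Working it through.** **Inputs from the article.** About 30 participants, 15 per intervention (Sample size). Significance level 0.05, taken as two-sided (Statistical methods). A round lasts four calendar weeks, weeks 0 to 3 (Table 2). Data collection runs from 3 September 2018 to 9 August 2019 (Trial status). There was no power calculation, so there is no stated figure to reproduce.

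**Assumed, because the article does not give them.** The number of rounds R, the ICC of change within a round, and the correlation ρ between a participant's baseline and post-intervention values.

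**Bound on R.** 340 days / 28 = 12.1, so at most about 12 rounds if they do not overlap. If week 3 of one round overlaps week 0 of the next, 340 / 21 = 16.2.

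**Step 1: pairing handled correctly, round ignored.** With m = 30/R participants per round, the variance of the contrast is understated by the design effect DE = 1 + (m − 1) × ICC, and the standard error by √DE. For R = 6 and ICC 0.05, DE = 1 + 4 × 0.05 = 1.20 and √1.20 = 1.10. Type I error was simulated with 40,000 trials per setting and no true difference, using a two-sample t-test on change scores:

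| Rounds | m | DE at ICC 0.05 / 0.10 / 0.20 | True type I error |
|---|---|---|---|
| 10 | 3 | 1.10 / 1.20 / 1.40 | 6.1% / 7.3% / 9.9% |
| 6 | 5 | 1.20 / 1.40 / 1.80 | 7.4% / 9.8% / 14.9% |
| 4 | 7 or 8 | 1.33 / 1.65 / 2.30 | 8.8% / 12.9% / 21.1% |

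With ten rounds and an ICC of 0.02 the error is 5.4%. With one block per intervention (R = 2) the contrast cannot be separated from calendar time, and no degrees of freedom are left to estimate variation between rounds.

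**Step 2: the model read literally.** If baseline and post-intervention are treated as independent samples, then for the intervention-by-time contrast, approximately,

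true SE / reported SE = √((1 − ρ) × DE).

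The reported interval is too narrow only if DE exceeds 1/(1 − ρ), which is 1.43, 2.0 and 3.3 at ρ = 0.3, 0.5 and 0.7.

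- ρ = 0.5, DE = 1.2: √0.60 = 0.77, so the interval is too wide.
- ρ = 0.7, DE = 1.65: √0.495 = 0.70, so the interval is too wide.
- ρ = 0.3, DE = 1.65: √1.155 = 1.07, so the interval is too narrow.

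Simulated over the settings of Step 1, type I error is about 3% to 12% at ρ = 0.3, 1% to 7% at ρ = 0.5 and 0.1% to 2% at ρ = 0.7. The main effect of intervention, which averages baseline with post-intervention, errs the other way: the ratio is √((1 + ρ) × DE), or √1.80 = 1.34 at ρ = 0.5 and DE = 1.2.

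**Step 3: what corrects it.** A t-test on round means of change held about 5% in every setting of Step 1. A random round intercept added to a two-row baseline/post model does not work. It adds the same amount to a participant's baseline and post-intervention values, so it cancels in the difference and leaves variation in change between rounds unmodelled. In a small check (150 runs, four rounds of 7, ICC 0.20, ρ = 0.5), that model still rejected about 22% of the time.

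**Step 4: price of the correction.** The reference distribution falls from 28 to R − 2 degrees of freedom. At ICC 0.05, including √DE, the 95% CI is wider than the one that ignores round by:

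- R = 10: (2.306 / 2.048) × 1.049 = 1.18 times
- R = 6: (2.776 / 2.048) × 1.095 = 1.48 times
- R = 4: (4.303 / 2.048) × 1.151 = 2.42 times

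**The case against.** **The written model usually errs towards caution on this contrast.** This stands. A reader might infer that every interval from the plan is too narrow, but the document does not support that. On the literal reading, the lost pairing outweighs the clustering in most settings at ρ = 0.5 and in all of them at ρ = 0.7. It does not rescue the plan, because an offset of unknown size is no control of error. It also disappears as soon as the analyst pairs the data properly, and the clustering error then shows in full.

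**The size rests on quantities that the article does not give.** This also stands. Individual sessions remove the dependence that group sessions would create, and taking change removes stable differences between rounds. With many small rounds and a low ICC the effect is slight.

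**The contrast is secondary and the article already urges caution.** This limits the importance of the point. The stated caution, however, concerns lack of power. It does not warn of dependence within rounds.

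**A fuller plan might add a round term.** It might, but the article does more than stay silent. It names a model, and that model does not match the allocation it describes.

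**The label is hedged as a variation.** This is fair, and the label is a wording point only. A reader might infer that the study claims the within-unit control of a stepped wedge. It does not: the same section says there is no control group, and no stepped-wedge analysis is planned. Nor does the article say that the future trial will run in single-intervention rounds, so it cannot be said that this trial must allow for a round component.

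**Conclusion.** The point holds in conditional form. Allocation is by round and the named analysis ignores round. With baseline and post-intervention correctly paired, the intervention-by-time p-values are too small and the 95% CIs too narrow if change varies between rounds. For assumed ICCs of 0.05 to 0.20, true type I error ranges from about 6% (ten rounds) to about 21% (four rounds). With the stated model taken literally, the direction can reverse. The safe conclusion is that the error bars for this contrast are unreliable in either direction.

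The correction is worth making because it is cheap, but it concerns a secondary, unpowered comparison and leaves the primary feasibility outcomes untouched. Calendar-time confounding (season, ward case-mix, staff experience) is a separate bias that no change to the error term removes.

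**What to change.** - **Statistical methods, Secondary dependent variables.** For the between-intervention contrast, analyse each participant's change (post-intervention minus baseline) with a random round effect and small-sample degrees of freedom, for example SPSS MIXED with Satterthwaite, or with a t-test on round means of change. If a two-row baseline/post model is kept, it needs a random round-by-time term as well as the participant effect; a random round intercept alone is not enough. The Scheirer-Ray-Hare fallback also assumes independent observations and should likewise give way to an analysis of change at round level.
- **Few rounds.** If either intervention has fewer than three rounds, report the contrast descriptively, without a p-value.
- **Design overview.** Replace the stepped-wedge label with a plain description: consecutive single-intervention rounds.

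The cost is analysis wording and a round identifier for each participant; no extra patients are needed. The downside is wider intervals and fewer degrees of freedom for this contrast (Step 4 of the working). The change does not deal with calendar-time confounding, which should be stated as a limitation.

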**Figure 2 F2:**
[figure not shown]
The independent variables of the proposed future clinical trial.

In order to ensure this present study is as scientifically valid as possible a number of precautions have been taken to protect the internal and external validity of the study within its methodological design: first, for each participant, all testing procedures (baseline and post-intervention (2 weeks)) will be conducted at approximately the same time of day (±2 hours). This will be controlled in order to protect the findings of the study from changes in the dependent variables which may be attributable to circadian variation rather than manipulation of the independent variables.^29^ The hypothesis of the study will not be divulged to participants prior to or during the conduction of the study in order to control for any potential degree of demand characteristics; a scenario where participants alter their behaviour and/or answers, in order to align with what they believe is potentially the ‘desired’ outcome of the study. All dependent variable testing sessions will take place at least 24 hours after the cessation of the previous training session for each participant. This will be implemented to ensure acute fatigue does not become a contributing factor to the results of the study, specifically relating to the secondary dependent variables, but also the feasibility of such practice during a proposed future clinical trial. The order in which dependent variables are tested will be counter-balanced throughout the study at each assessment timepoint in order to attempt to protect the study from practice effects, especially order effects, where a participant has been exposed to a specific order of testing before and as such performs better on subsequent testing procedures of the same material. Additionally, only one intervention will be run at a given time, protecting against potential subconscious selection bias among the research team relating to group allocation of participants. Finally, in order to increase the external validity of the study, eligibility criteria will be kept as minimalistic as possible (within the limits of safety and reason), in order to allow as inclusive a proportion of this population as possible, and in such producing findings which are applicable to not only those within the study, but to the greater population of frail geriatric hospital inpatients and particularly those within delayed transfer of care settings.

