#### Secondary dependent variables

The secondary dependent variables relating to multidimensional health (comprising the proposed primary dependent variables of the future clinical trial) will be:

Physiological*: serum cortisol, dehydroepiandrosterone-sulphate (DHEAS), cortisol: DHEAS ratio, C reactive protein (CRP), IL-6, tumour necrosis factor alpha (TNFα), interferon gamma (IFNγ).

Functional: hand grip strength (Southampton protocol,^34^ Leg strength and power output,^35 36^ Short Physical Performance Battery (SPPB),^37^ Katz Index of Independence in Activities of Daily Living (Katz ADL),^38^ and the Fried Frailty Phenotype)^2^

Psychological/emotional: Geriatric Depression Scale,^39^ Hospital Anxiety Depression Scale.^40^

Cognitive: Standardised Mini-Mental State Examination.^41^

Social: Interpersonal Support Evaluation List (ISEL-12).^42^

*All blood samples will be obtained through venepuncture. Serum will be analysed for the physiological dependent variables relating to cortisol, DHEAS and CRP (assessed by commercial ELISA kit). Inflammatory cytokines (IL-6, TNFα, IFNγ) will be assayed using a multiplex commercial kit (R&D Systems). These specific physiological variables will be examined due to their association with the ageing process, and previous research which have both proposed and indicated that exercise is potentially capable of altering these variables.^43–48^

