#### Baseline assessment

Participants’ baseline sociodemographic and information for the secondary dependent variables will be collected between 5 and 2 days prior to intervention commencement. 1RM for the specially adapted resistance training equipment will also be assessed during this time period (after all baseline testing has been completed, and at least 24 hours after baseline testing which requires physical exertion, which may impact on the accuracy of the 1RM measurements). 1RM will be determined based on estimation from participants five repetition maximum (5RM) utilising the Epley formula: 1RM=w (1+r/30), where 1=weight, and r=repetitions.^36^ The protocol employed during obtainment of participants 5RM has been adapted from^35^ (online supplementary file 1). A balance screening will also be conducted prior to the commencement of the MIOLI intervention to determine whether participants should perform exercises standing, standing with chair support, or seated. In addition, the resistance bands which participants in the MIOLI intervention will use will similarly be assessed during this period; with three options corresponding to light, moderate and high resistances, prescribed to participants based on their initial ability and preference during their performance of the exercises in which the resistance bands will be utilised.

10.1136/bmjopen-2019-031159.supp1Supplementary data

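### Counter-balancing test order at each visit adds avoidable within-person noise to the baseline-to-post change, and it cannot remove retest gain from that change

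*Protocol article*

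**What the plan says.** In the Design overview, among the precautions for internal validity, the protocol article states: "The order in which dependent variables are tested will be counter-balanced throughout the study at each assessment timepoint". The purpose given is "in order to attempt to protect the study from practice effects, especially order effects", explained as a participant who, having met an order of testing before, "performs better on subsequent testing procedures of the same material".

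The variables covered are those under Secondary dependent variables. They include blood measures ("Physiological*: serum cortisol, dehydroepiandrosterone-sulphate (DHEAS), cortisol: DHEAS ratio, C reactive protein (CRP), IL-6", plus TNFα and IFNγ) and physical tests (grip strength, leg strength and power, SPPB). On sampling, that section says "All blood samples will be obtained through venepuncture" and does not place the draw within the test order.

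Two neighbouring rules deal with exertion:

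- The Design overview keeps every testing session at least 24 hours clear of the previous training session: "This will be implemented to ensure acute fatigue does not become a contributing factor to the results of the study".
- The Baseline assessment section puts 1RM after all other baseline testing and "at least 24 hours after baseline testing which requires physical exertion", because exertion could make the 1RM less accurate. The Post-intervention assessment section shows only the 24-hour gap after training.

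There are two main timepoints (Data collection), no control group (Design overview) and about 15 participants per intervention (Sample size). The analysis compares baseline with post-intervention across the two interventions (Statistical methods).

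**The concern.** The efficacy signal is each participant's change between two visits, so conditions should match within a person. The protocol follows that principle for time of day, which it holds to within 2 hours. Varying the test order at each timepoint works against it. If blood is drawn in the same session as exertional tests, a participant may be sampled after exertion at one visit and before it at the other. The same applies to a performance test that follows other exertional tests at only one visit. Any acute effect of exertion then enters the change score.

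The second issue is the benefit claimed. Improvement on a second exposure to the same test is a retest gain. Reordering tests within a visit does not alter which exposure is the second one.

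Both matter mainly for what comes next. These variables are the proposed primary outcomes of the future trial, and the estimates are meant to inform its design. Inflated change variance and an unacknowledged retest gain would carry forward.

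**Working it through.** The protocol gives no figure on this point and made no power calculation, so there is nothing to reproduce. The arithmetic below is illustrative.

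**Inputs.** From the protocol: two timepoints, about 30 participants, 15 per arm, no control group, and three exertional tests (grip, leg strength/power, SPPB). Assumed: prior exertion shifts a marker by d SD, however many tests precede the draw; the pre-post correlation is ρ = 0.7; and blood shares a session with k exertional tests.

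**1. How often the two visits differ.** If blood is equally likely to fall in any position, the chance that it follows at least one exertional test is p = k/(k+1). With independent orders at the two visits, the share of participants whose visits differ is 2p(1−p).

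| k | p | Share differing | Of 30 |
|---|---|---|---|
| 1 | 0.50 | 0.50 | 15 |
| 2 | 0.67 | 0.44 | 13.3 |
| 3 | 0.75 | 0.375 | 11.2 |
| 4 | 0.80 | 0.32 | 9.6 |

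If blood is always first, the share is 0. If a 50:50 order is reversed at the second visit, it is 1.

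**2. Variance added to the change.** A participant whose visits differ gains or loses d, with equal probability when orders are balanced. The added variance is therefore d² × (share differing). Without order variation the change variance is 2(1−ρ) = 2 × 0.3 = 0.6.

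| Case | Added variance | d = 0.3 | d = 0.5 |
|---|---|---|---|
| Three exertional tests, random order | 0.375 d² | 0.034/0.6 = 6% | 0.094/0.6 = 16% |
| 50:50 at each visit (maximum for independent orders) | 0.5 d² | 0.045/0.6 = 8% | 0.125/0.6 = 21% |
| 50:50, reversed between visits | d² | 0.09/0.6 = 15% | 0.25/0.6 = 42% |

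**3. Effect on an arm mean.** The expected shift is zero when orders are balanced at both visits. At d = 0.5 and n = 15, order alone contributes a random shift with SD √(0.375 × 0.25/15) = 0.08 for three tests in random order, and √(0.25/15) = 0.13 for the reversed order.

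**4. Retest gain.** Write the mean change as δ + g + (mean position effect at post − mean position effect at baseline), where δ is the intervention effect and g the retest gain. The bracket averages to zero under balanced orders, and also under a fixed order. In both cases δ + g remains. With δ = 0 and an assumed g = 0.30 SD, the mean change is 0.30 SD either way. In the intervention-by-time interaction the contrast is (δ₁ + g₁) − (δ₂ + g₂), so the gain drops out only if g₁ = g₂.

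**5. The 1RM rule against the order rule.** The leg strength and power outcome cites the same two sources as the 5RM/1RM procedure. If they are the same test, at baseline it always comes last and rested, which is not counter-balancing. No matching rule is shown for the post visit. The baseline value could then be rested and the post value not, a difference in one direction rather than noise. The article does not say whether they are the same test.

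**The case against.** Four points on the other side carry weight.

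- **Shared sessions are not stated.** Assessment runs from Wednesday to Saturday in week 0 and Monday to Saturday in week 3 (Table 2). Blood could be drawn on a separate day, and the full protocol may say so. This stands, and it makes the noise conditional. The order rule as written still exempts nothing.
- **The 24-hour rules are narrower than they look.** One concerns training sessions and the other the accuracy of 1RM. A reader might infer that the protocol itself regards brief testing as contaminating serum markers. It does not say that. It says exercise may alter the markers, without distinguishing acute from longer-term effects.
- **Counter-balancing has real value.** It averages within-session order effects, and the text claims only an attempt, with emphasis on order effects. To say that it protects against nothing would be wrong. What does not stand is extending the claim to better performance on repeat testing.
- **The consequence is limited.** The added noise is reflected in the residual error and the confidence intervals, the primary analysis is qualitative, and the article already asks for caution on efficacy.

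A reader might also conclude that everyone needs one universal test order, or that machine-based leg strength should give way to SPPB when the arms are compared. Neither follows. Matching order within each person is enough for the first. The second concerns training specificity, which no test order addresses.

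**Conclusion.** The point holds in a limited form. As written, the order rule lets blood or a performance test follow exertion at one visit and precede it at the other, if they share a session. With three exertional tests in random order, the cost is about 6% to 16% more change variance for d between 0.3 and 0.5. Both d and ρ = 0.7 are assumptions that the documents neither support nor exclude. It is tempting to read this as bias in the marker results, but with orders balanced at both visits the documents support only noise and chance imbalance in arms of 15.

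The retest point needs no assumed size: with two visits and no control group, any gain stays in the baseline-to-post effect under every test order. The 1RM inconsistency depends on whether 1RM is the leg-strength outcome.

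Severity is minor, because these are secondary outcomes of an unpowered feasibility study.

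**What to change.** - Exempt blood from counter-balancing and draw it before any exertional test at both visits.
- If order is varied for the remaining tests, vary it between participants and keep each participant's own order identical at baseline and post-intervention.
- State whether 1RM is the leg-strength outcome. If it is, reconcile the Design overview with the Baseline assessment section so that both visits use the same position and the same rest interval.
- Limit the stated benefit of counter-balancing to order effects. Add that retest gain remains in the baseline-to-post change and cancels in the intervention-by-time interaction only if it is equal in both arms.

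The cost is a small procedural constraint and a few lines of text, with no extra tests. Carry-over between tests cancels in the change score only if it is similar at both visits, and ten training sessions might alter how tiring the tests are. The trial began in September 2018, so a change made during recruitment should apply only to participants not yet assessed at baseline. For the others, the order used at each visit should be reported.
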